### Safety Monitoring: Because increases in serum creatinine and CK levels have been reported in some people using creatine (7,27), these parameters will be monitored every other week. If serum creatinine levels increase to above 1.8 mg/dl or CK increases to > 450 U/liter in men or 400 in women (ULN 226 in men and 140 in women), study medication will be held for one week. If, after one week, creatinine and/or CK levels have returned to baseline levels, study medication will be resumed at half of the initial dosing level and creatinine and/or CK levels monitored weekly. If creatinine and/or CK levels again exceed the aforementioned values on this reduced dosing regimen, study drug will be discontinued and the subject followed on a biweekly basis until these levels return to within acceptable limits.

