#### **F. Experimental protocol:**

**1. Screening:** The assessment of eligibility will include a medical history targeted to HIV and cardiovascular disease; physical examination; exercise, weight, and antiretroviral history; electrocardiogram;current medication inventory; and nutritional assessment by 24-hour recall. Blood samples will be collected for standard chemistries and hematology to exclude subjects with any significant laboratory abnormality as listed above.

**2. Baseline assessments:** Eligible subjects will undergo baseline testing that includes measurements of muscle cross-sectional area and isometric strength, fatigue and metabolism; dynamic strength of knee and ankle flexors and extensors; habitual physical activity; and total and regional body composition. Blood samples will be collected for measurement of lipids and lipoproteins, glucoregulatory, gonadal, and adrenal hormones, viral load, and indices of immune function. Subjects will prepare a 3-day food intake diary to quantitate baseline energy and macronutrient intake and meat consumption.

**3. Randomization:** Subjects will then be randomized, in a 1:1 fashion, to receive either creatine or placebo, following the dosing regimen described below. Between the 12th and 14th day after randomization, subjects will repeat all of the measurements performed at baseline except for physical activity and food intake. All subjects will then begin a 12-week progressive resistance exercise program, consisting of 3 training sessions per week. Subjects will remain on their assigned oral study regimens (creatine or placebo) during these 12 weeks.

**4. Creatine Dosing:** Although current dosing regimens for creatine supplementation are known to vary widely in the community, we have selected a dosing regimen based on loading, maintenance, and rest cycles used by creatine manufacturers and experts in the use of creatine for athletic training. The loading dose is a total of 20 g pure creatine monohydrate or placebo in capsules, taken in four divided dosesdaily with a non-caffeinated solution containing 20 g of simple carbohydrate. This regimen will be followed for 5 consecutive days, after which subjects will begin maintenance dosing of 4.8 g daily. Maintenance dosing will continue for five weeks, after which this cycle of loading and maintenance will begin again.

**5. Procedures:** Unless noted otherwise, all procedures will be performed in the GCRC at SFGH.

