**G. Risks and Discomforts**

**1. Side Effects of Medications:** Serum creatinine levels may increase slightly with creatine therapy, although there have been no reports of overt renal dysfunction except for one case in which the subject had underlying nephrotic syndrome and glomerulosclerosis (28). Transient muscle cramps and elevation in circulating creatine kinase levels have also been reported (7,27). Some subjects taking creatine supplements have complained of nausea, stomach upset, dizziness or weakness, loose stools, or diarrhea at daily serving sizes greater than 5 grams (6,7). As described above, we will monitor serum creatinine and CK levels and reduce or discontinue dosing with study medication if warranted.

**2. Exercise and Strength Testing:**  Resistance exercise and muscle strength testing may result in muscle fatigue or soreness. Joint discomfort may be experienced if the exercises are not performed correctly. To minimize these risks, the starting resistance used will be individualized according to strength and tolerance and progression of the program will be gradual. In addition, all training will be monitored by an ACSM certified Exercise Specialist.

**3. Magnetic Resonance Spectroscopy/Imaging:** There are no significant risks associated with the MRS measurements, aside from the possibility of a magnetic object being pulled into the magnet. However, precautions have been taken to prevent such an event from happening; loose metal objects such as jewelry, pocket knives, or key chains, are not allowed in the MRS room. The subject may become fatigued from prolonged sitting in the magnet, and relatively small amounts of discomfort might be experienced when the subject is asked to exercise his/her limb for a prolonged period of time. Some soreness in the muscles may appear after muscle testing, but this will be slight, will not impede normal daily activity, and will subside within a few days. For the MRI portion of the study, subjects may be bothered by feelings of claustrophobia and by the loud noise during this part of the study. Temporary hearing loss has been reported, so subjects will be asked to wear ear plugs.

**4. Radiation Exposure***:* Exposure from DEXA is less than 5 mrem per measurement, which is less than 1% of the exposure from a chest X-ray. The stable isotope 2H (deuterium) contains no radioactivity and has no recognized adverse effects.

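### The restart dose after a creatinine or CK hold is tied to an undefined initial level; one plain reading gives 10 g/day, about twice the maintenance dose, although the protocol calls it a reduction

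*Protocol*

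**What the plan says.** Section F.4 (Creatine Dosing) and Attachment 3 describe two dose levels. Treatment opens with the load: "The loading dose is a total of 20 g pure creatine monohydrate or placebo in capsules". The step down follows: "This regimen will be followed for 5 consecutive days, after which subjects will begin maintenance dosing of 4.8 g daily". F.4 then gives five weeks of maintenance before the cycle restarts. Attachment 3 marks loads in weeks 1-2, 7-8 and 13-14.

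Safety Monitoring has creatinine and CK checked every two weeks and holds drug for one week when a limit is crossed. If values return to baseline, "study medication will be resumed at half of the initial dosing level", with weekly checks from then on. The following sentence covers a second crossing, when levels "again exceed the aforementioned values on this reduced dosing regimen", and stops drug in that case.

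Section G.1 (Side Effects of Medications) states the purpose of the monitoring: "we will monitor serum creatinine and CK levels and reduce or discontinue dosing with study medication if warranted".

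No passage defines the initial level, gives the restart dose in g/day, or says how a scheduled load applies to a subject who has restarted.

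**The concern.** The restart rule takes half of one level in a regimen that has two. The first dose that every subject receives is the load, so a reader who applies the words as they stand halves 20 g/day. For a subject whose limit was crossed on 4.8 g/day, the result is more drug after the safety signal than before it. That conflicts with the next sentence of Safety Monitoring and with G.1, both of which present the restart as a reduction.

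Two things are at stake. The first is subject protection: a rule meant to lower exposure after a renal or muscle signal can be followed to the letter and raise it. The second is interpretation. With 20 subjects per group, exposure within the creatine arm after a hold would depend on how the person applying the rule read one word.

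**Working it through.** **Inputs.** Load 20 g/day for 5 days; maintenance 4.8 g/day for five weeks (35 days), then repeat (F.4, Attachment 3). Hold of 7 days; checks every two weeks (Safety Monitoring). Scheduled on-treatment checks at weeks 2, 4, 6, 8, 10, 12 and 14, that is days 14, 28, 42, 56, 70, 84 and 98 (Attachment 2). The protocol gives no restart dose in grams, so there is no stated figure to reproduce.

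**Step 1: the restart dose under each reading.**

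| Meaning of *initial* | Hold during maintenance | Hold during a load |
| --- | --- | --- |
| First dose given (20 g/day) | 20/2 = 10 g/day | 20/2 = 10 g/day |
| Level in force before the hold | 4.8/2 = 2.4 g/day | 20/2 = 10 g/day |

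- First reading against maintenance: 10/4.8 = 2.08, so the dose roughly doubles.
- Between readings, for a maintenance hold: 10/2.4 = 4.17, about 4.2-fold.
- For a hold during a load the readings agree, and 10 g/day is below the 20 g/day then in force.

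**Step 2: how often a check falls in maintenance.** Three loads of 5 days make 15 of 98 days, so maintenance covers (98 - 15)/98 = 85% of treatment. The check days themselves are:

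- *Cycle in F.4:* 5 + 35 = 40 days, so loads fall on days 1-5, 41-45 and 81-85. Days 42 and 84 are in a load and the other five checks are in maintenance: **5 of 7**.
- *Attachment 3, assuming that each load opens its two-week block:* loads fall on days 1-5, 43-47 and 85-89. No check day is in a load: **7 of 7**.

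The week-14 check coincides with the end of treatment, so a restart can follow only the first six. Of those, 4 of 6 (F.4) or 6 of 6 (Attachment 3) are in maintenance.

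**Step 3: later loads.** A subject held at week 2 or week 4 who restarts still has the second load ahead. Under the Attachment 3 assumption, a hold triggered on day 42 runs over days 43-49 and covers the whole load of days 43-47. Safety Monitoring does not say whether such a load is given in full, reduced or omitted. A 7-day hold also outlasts a 5-day load, so a subject held in a load would, if the calendar keeps running, restart when maintenance is scheduled. The protocol does not say whether the calendar pauses.

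**The case against.** The strongest reply is that *initial* need not mean the load. F.4 and Attachment 3 use the terms loading and maintenance, and the restart rule uses neither. Set against the reduced regimen of the next sentence, *initial* can mean the regimen in force before the hold. Each phase is then halved, the word *reduced* is true throughout, and if the whole regimen is meant, later loads are halved as well. G.1 supports that intent. This stands as a fair reading, and a careful clinician may well adopt it. It does not remove the problem, because nothing in the protocol chooses between the readings and the words taken at face value give the other answer.

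The second reply is that there are safeguards. Drug restarts only after values return to baseline, checks then become weekly, a second crossing ends treatment, and entry criteria exclude creatinine above 1.5 mg/dl and CK above 1.5 times ULN. These limit how long a misreading could go unnoticed. They do not tell anyone what dose to dispense.

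A reader might also infer that nearly every hold would meet the contradiction, or that discontinuation rates would differ by reading. The documents support neither. Under the F.4 cycle two of the seven checks fall in a load, where both readings lower the dose, and the protocol gives no expected number of holds or second crossings.

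**Conclusion.** The point holds as an undefined term in a safety rule, with one plain reading that contradicts the protocol's own text. A reader might go further and conclude that the protocol prescribes a higher dose after toxicity. It does not: the load is never named as the initial level, and the protocol's stated intent is to reduce.

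Its size is a restart dose of either 10 or 2.4 g/day for a subject held in maintenance, where most scheduled checks fall. The 5-of-7 count takes the F.4 cycle at face value; the 7-of-7 count assumes that each load opens its Attachment 3 block. Both assume checks on the nominal days. The silence on later loads is a separate gap; it closes only if the rule is taken to halve the whole regimen, which the text does not say.

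This goes beyond detail that could be left to a later document. The rule acts on individual subjects, and followed literally it can do the opposite of what the protocol says it does. It should be corrected.

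**What to change.** Reconcile Safety Monitoring with F.4, G.1 and Attachment 3 so that the protocol:

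- states the restart level in g/day, separately for a hold that begins in a load and one that begins in maintenance;
- makes that level a reduction in every case, as Safety Monitoring and G.1 already say it is;
- says what happens at later loading periods for a subject who has been held or has restarted, and whether the dosing calendar pauses during a hold.

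The figures are for the sponsor's clinical lead to set, and none is proposed here. The cost is one or two sentences in a protocol amendment, with no change to sample size, visits or analysis.

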**G. Risks and Discomforts**

**1. Side Effects of Medications:** Serum creatinine levels may increase slightly with creatine therapy, although there have been no reports of overt renal dysfunction except for one case in which the subject had underlying nephrotic syndrome and glomerulosclerosis (28). Transient muscle cramps and elevation in circulating creatine kinase levels have also been reported (7,27). Some subjects taking creatine supplements have complained of nausea, stomach upset, dizziness or weakness, loose stools, or diarrhea at daily serving sizes greater than 5 grams (6,7). As described above, we will monitor serum creatinine and CK levels and reduce or discontinue dosing with study medication if warranted.

**2. Exercise and Strength Testing:**  Resistance exercise and muscle strength testing may result in muscle fatigue or soreness. Joint discomfort may be experienced if the exercises are not performed correctly. To minimize these risks, the starting resistance used will be individualized according to strength and tolerance and progression of the program will be gradual. In addition, all training will be monitored by an ACSM certified Exercise Specialist.

**3. Magnetic Resonance Spectroscopy/Imaging:** There are no significant risks associated with the MRS measurements, aside from the possibility of a magnetic object being pulled into the magnet. However, precautions have been taken to prevent such an event from happening; loose metal objects such as jewelry, pocket knives, or key chains, are not allowed in the MRS room. The subject may become fatigued from prolonged sitting in the magnet, and relatively small amounts of discomfort might be experienced when the subject is asked to exercise his/her limb for a prolonged period of time. Some soreness in the muscles may appear after muscle testing, but this will be slight, will not impede normal daily activity, and will subside within a few days. For the MRI portion of the study, subjects may be bothered by feelings of claustrophobia and by the loud noise during this part of the study. Temporary hearing loss has been reported, so subjects will be asked to wear ear plugs.

**4. Radiation Exposure***:* Exposure from DEXA is less than 5 mrem per measurement, which is less than 1% of the exposure from a chest X-ray. The stable isotope 2H (deuterium) contains no radioactivity and has no recognized adverse effects.

**5. Venipuncture:** Venipuncture and placement of intravenous lines may result in a hematoma, which can be painful but carries no significant risks. Infections from IV lines rarely occur from such brief placements. However, any signs of inflammation will lead to removal of the catheter and treatment with heat and elevation.

**6. Phlebotomy:** The total amount of blood drawn will not exceed 200 cc.

**H. Treatment and Compensation for Injury:** If a subject is injured as a result of being in this study, treatment will be available. The cost of such treatment may be covered by the University of California. Subjects will be informed that they may obtain further information by calling the Committee on Human Research.

**I. Alternatives:** Subjects may choose not to participate in the study.

**J. Costs to the Subject:** There will be no charges to the subject. The costs of the study medication and all tests required for the study will be covered by the study. Transportation costs to and from the VAMC will also be reimbursed or covered by taxi vouchers.

**K. Reimbursement of Subjects:** Subjects will be reimbursed $1,000 for completing the study. Subjects who do not complete the full study will be reimbursed $200 for each major assessment (baseline and week 2).

**L. Confidentiality of Records:** Participation in research may involve loss of privacy. The subjects' research records will be handled as confidentially as is possible within the law. All records will be coded and stored in the office of the PI. Copies of the signed consent forms are kept by the GCRC, the subjects, and the PI. Copies of the subjects’ medical records may be reviewed by representatives of the Food and Drug Administration. No individual identities will be used in any reports or publications resulting from this investigation.

**5. QUALIFICATIONS OF INVESTIGATORS:** Over the past six years, Drs. [name] and [name] have conducted numerous studies of anabolic and anticytokine therapies and their metabolic effects in HIV-infected individuals with weight loss, as well as studies of body composition and energy metabolism in groups of men and women with HIV infection. [name] has performed numerous studies of muscle metabolism and function in subjects with a variety of chronic catabolic conditions or neuromuscular disorders.

**6. BIBLIOGRAPHY:** attached.

**Attachment 2. Study timetable**

|  | | *Creatine or placebo throughout study* | | | | | | | | |
| --- | --- | --- | --- | --- | --- | --- | --- | --- | --- | --- |
|  | | | | ***Progressive resistance exercise 3X weekly beginning at week 3*** | | | | | | |
|  | 0 | | Wk 2 | Wk 4 | Wk 6 | Wk 8 | wk 10 | Wk 12 | wk 14 |  |
| 1 Repetition Max | X | | X | X | X | X | X | X | X |  |
| MRI | X | | X |  |  |  |  |  | X |  |
| MRS | X | | X |  |  |  |  |  | X |  |
| Total body water | X | | X |  |  |  |  |  | X |  |
| Accelerometer | X | |  |  |  |  |  |  | X |  |
| DEXA | X | | X |  | X |  | X |  | X |  |
| Anthropometry | X | | X |  | X |  | X |  | X |  |
| 3-day food intake diaries | X | |  |  |  |  |  |  | X |  |
| Serum creatinine, CK | X | | X | X | X | X | X | X | X |  |
| Chemistries | X | | X |  | X |  | X |  | X |  |
| Hematology | X | | X |  | X |  | X |  | X |  |
| Hormones | X | | X |  |  |  |  |  | X |  |
| Virology | X | | X |  |  |  |  |  | X |  |
| Immunology | X | | X |  |  |  |  |  | X |  |

##### Attachment 3: Creatine dosing regimen

- Loading dose: 20 g/day pure creatine monohydrate powder or placebo in capsules (in four divided doses). Each dose will be taken together with a non-caffeinated solution containing 20 g of simple carbohydrate . This regimen will be followed for 5 consecutive days, after which patients will begin maintenance dosing.
- Maintenance dose: 4.8 g/day pure creatine monohydrate powder or placebo in capsules (in two divided doses), to be taken with a non-caffeinated carbohydrate solution as specified above.

|  | *Wks 1-2* | **Wks 3-4* | *Wks 5-6* | *Wks 7-8* | *Wks 9-10* | *Wks 11-12* | *Wks 13-14* |
| --- | --- | --- | --- | --- | --- | --- | --- |
| *CREATINE/ PLACEBO* |  |  |  |  |  |  |  |
| Load | X |  |  | X |  |  | X |
| Maintenance | X | X | X | X | X | X | X |

**** Exercise regimen begins and continues for 12 weeks***
